#### 2.8.3. Delivery and Early Postpartum

After delivery, umbilical cord blood will be collected for the measurement of C-peptide and stored in the biobank to allow future analyses of metabolomics, provided informed consent is present. Neonatal skinfold thickness measurement will be performed within 72 h after birth. The measurement will be performed by trained study staff using a Harpenden skinfold calliper, as previously described in the HAPO study [33]. Neonatal body fat mass will be determined according to a validated formula [25]. Maternal outcomes will be collected until maternal discharge; neonatal outcomes will be collected until neonatal discharge, which may occur jointly or separately.

#### 2.8.4. Biochemical Parameters and GDM Screening

Lab measurements will be performed in line with normal routine. Based on recommendations for micronutrient monitoring during pregnancy after MBS, vitamin A (µg/L), 25-OH-Vitamin D (µg/L), vitamin B12 (ng/L), folate (µg/L), prothrombin time (s, %, INR), iron (µg/dL), transferrin saturation (%), and ferritin (µg/L) will be measured every trimester in the surgical group [34]. Micronutrient monitoring in the control group will be conducted based on clinical judgement.

At first prenatal visit, screening for overt diabetes will be performed using fasting plasma glucose (FPG, mg/dL), or HbA1c (%) if fasting is not feasible. Women with a history of bariatric surgery will undergo screening for GDM at 24–28 weeks of pregnancy and will perform SMBG for a maximum of one week, as previously described [34]. At 24–28 weeks, the control group will be screened using a 50 g glucose challenge test. However, women with a history of GDM, obesity, or impaired fasting glycaemia in early pregnancy will undergo a 75 g OGTT, according to the 2019 Flemish guidelines [35]. An overview of diagnostic criteria for GDM in both groups is provided in Supplemental Table S1.

Specifically for this study and for all participants, at each study visit (6–12 weeks, 18–22 weeks, 24–28 weeks, and 30–34 weeks) and at delivery when cord blood is collected, two additional plasma samples will be collected for long-term storage at the biobank of UZ Leuven to allow for future analysis of metabolomics.

#### 2.8.5. Clinical Measurements

Blood pressure will be measured using a calibrated automatic blood pressure monitor. Height will be measured to the nearest 0.5 cm using a calibrated wall-mounted stadiometer. Weight will be measured to the nearest 0.1 Kg using a calibrated digital scale. BMI will be calculated as kg/m^2^. Waist circumference will be measured to the nearest 0.1 cm by applying the tape directly on the skin, horizontally at the level that is midway between the iliac crest and the lowest lateral portion of the rib cage. Body composition will be measured by bioelectrical impedance analysis with Bodystat 1500^®^ (Bodystat Ltd., Douglas, Isle of Man, UK).

#### 2.8.6. Food Diary

To assess the baseline dietary habits, a 3-day dietary record will be used, as it provides a more accurate reflection of habitual intake compared to shorter or longer periods, which are prone to misreporting. Ideally, the records will be collected on non-consecutive days [36]. For Dutch-speaking participants, the Digitaal Dagboek^®^ app will be used. This mobile application is developed by UCLL (University of Applied Sciences, Leuven, Limburg, Belgium) and is specifically designed for participants in scientific research studies. Each participant will receive a study-specific login linked to their unique subject identification number, ensuring that the study team can only access data relevant to the specific study. For the GLORIA study, participants will be able to log both prepared meals and store-bought products. The algorithm of the app will calculate daily intake of macro- and micronutrients based on their entries. For non-Dutch-speaking participants or those unable to use the app, a written food diary will serve as an alternative method of dietary data collection.

#### 2.8.7. Biobank

Participants will provide explicit consent regarding the storage of their biological material for future research. The obtained blood samples will be transported by a courier to the biobank of UZ Leuven at least every three months. Samples will be archived at the biobank UZ Leuven at −80 °C for a maximum of 10 years post-study, contingent on affirmative consent. Samples will be used in the GLORIA research project, which is fully independent of any commercial involvement. These samples either alone or in combination with the collected data can be used for further research, on the condition that this is related to the current study. Future use will require definition of the research purpose and prior ethics committee approval.

#### 2.8.8. Cord Blood

Venous cord blood (3 samples) will be collected at delivery in each participating centre by a midwife or obstetrician. Cord-blood will be obtained by free drainage (free flow) or drawn by needle aspiration (puncture) from a clamped segment of an umbilical vein. In each centre, cord blood will be stored locally at −20 °C and transported to UZ Leuven for storage at −80 °C at the biobank of UZ Leuven until analyses. Samples will be stored for max. 10 years.

#### 2.8.9. CGM

The Dexcom G6^®^ CGM system with blinded receiver (Dexcom, San Diego, CA, USA) is a CE-labelled device that is approved for use in pregnancy [37] and provides real-time continuous measurement of interstitial glucose levels via a small sensor, which is inserted in the subcutaneous skin of the abdomen or upper arm. The device is disposable and without the need for calibrations. One sensor session can record glucose values for up to 10 days. This sensor has a high accuracy, as reflected by the mean absolute relative difference (MARD) of 8.7% for wear on the posterior upper arm in pregnancy [37]. CGM will be performed at four distinct timepoints, each involving a single sensor session. Continuous CGM throughout the entire pregnancy was not pursued due to the substantial cost implications for this investigator-initiated academic trial. Additionally, continuous monitoring would likely increase participant burden, potentially affecting recruitment, adherence, and retention. The study design was therefore optimised to align with routine clinical care. Of note, previous research in uncomplicated pregnancies has demonstrated that CGM-derived metrics remain relatively stable across all three trimesters. The Dexcom G6^®^ sensor will be used in a blinded manner, so that glucose values are masked from the participant to encourage normal daily behaviour and obtain unbiased insights into maternal glucose patterns. This approach avoids potential issues associated with unblinded CGM, which may inadvertently cause anxiety, disrupt sleep, and lead to unnecessary carbohydrate intake in response to device-alerted hypoglycaemia. Such behaviours could influence participant responses and provoke post-bariatric hypoglycaemia, thereby biassing glucose data. Furthermore, the clinical significance of hypoglycaemia detected by CGM during pregnancy after MBS is not well established.

#### 2.8.10. Ultrasound Measurements

To evaluate foetal anatomy, growth, body composition, and placental function, detailed ultrasound examination according to current ISUOG guidelines will be performed by trained sonographers at approximately 12, 20, and 32 weeks of gestation (Table 1). Training of the sites will be provided by an obstetrician from UZ Leuven, who has extensive experience in ultrasound measurements in pregnant women with obesity and after bariatric surgery.

Participating centres will detach dedicated sonographers trained in routine sonographic measurements. For specific study measurements including FASTT, detailed standard operating procedures (SOPs) will be available to the research teams. Training sessions will be organised. Digital images of foetal measurements will be stored. In the data management phase, we will evaluate measurements by individual sonographer and study centre to further exclude abnormal variability (both internal and external).

#### 2.8.11. Metabolomics

The metabolomics and data analyses will be performed by the Systems Medicine Department from the Steno Diabetes centre (Copenhagen, Denmark). This lab has extensive expertise on non-targeted and targeted metabolomics and has previously shown evidence of metabolomics profile shift in diabetes complications [38]. In addition, their research group includes experts in bioinformatics to manage data from metabolomics. Cord-blood and maternal plasma samples will be collected at different time points (Table 1) and will be stored in the biobank of UZ Leuven at −80 °C before shipment to the lab of the Steno Diabetes centre. Based on a pilot study of West K et al. showing that changes in metabolites were most significant in late pregnancy [16], we will prioritise the analysis of metabolomics on maternal plasma collected at 30–34 weeks of pregnancy [16]. Since there is limited evidence that shifts in maternal metabolic profile induced by malabsorptive surgery are associated with reduced birth weight of their offspring [16], a lipidomics platform and a metabolism platform (as further described below) will be used. Based on the sample size from the pilot study (25 with RYBG and 8 SG), plasma samples from at least 60 women (30 with RYBG and 30 with SG) will be analysed and compared to at least 60 women from the control group. As metabolomics is a discovery-driven methodology, a formal power calculation was not possible due to limited existing data (the pilot study only reports changes in relative concentrations of metabolites without information on variability, and non-specific methods were used to evaluate metabolites). The SGA metabolic profile of bariatric women will be correlated as meta-analysis with publications focused on metabolic mechanisms of foetal growth retardation in populations without bariatric surgery to evaluate the impact of the surgical procedure [39]. To take into account dietary factors, the Frequency Food questionnaire [29] and data on the timing and content of the last meal before each blood sample will be collected.

Lipidomics platform: This method measures molecular lipids by ultra-high-performance liquid chromatography coupled to a quadrupole time-of-flight mass spectrometer and can be used for analysing plasma and tissue samples. Lipidomics enables the detection of approximately two thousand metabolic features and identification of 300 to 900 molecular lipids (representing the most important lipid groups, e.g., phospholipids, lysophospholipids, ceramides and sphingolipids, di- and triacylglycerols). Metabolism and Energy platform: The citric acid cycle, short-chain fatty acids, and ketones to identify up to 120 metabolites that are metabolised by both the liver and gut can be measured with gas chromatography. Then, utilising ultra-high-pressure liquid chromatography tandem mass spectrometry (UHPLC-MS-MS) near thirty-six metabolites including amino acids and related metabolites, polar metabolites, and small organic acids will be quantified; this platform is targeted and specifically designed for metabolic syndrome biomarkers. Pre-processing and statistical analysis: The data pre-processing pipelines of the metabolomic platforms are based on bioinformatic tools that automatically detect metabolite signals from the measurement mass chromatograms and associate the signals with known metabolites based on their mass-spectrometric fingerprint using in-house molecule libraries. Metabolites will be identified using semi-quantification and tandem mass spectrometry fragmentation patterns and tested for over-representation of functional annotations. Multivariate analyses will identify metabolites, ratios, and combinations of metabolites associated with clinical outcomes. Bonferroni correction will be used for multiple test correction.

### 2.9. Statistics

This study examines the association between glycaemic patterns during pregnancy after MBS and birth weight. The primary aim is to assess whether glycaemic dysregulation (e.g., hypoglycaemia, glycaemic variability) contributes to foetal growth restriction in this population.

#### 2.9.1. Sample Size and Power Calculation

The sample size (n = 95) was calculated based on the best available data on CGM in pregnancy with MBS [40,41]. The study provides 80% power to detect a moderate association (effect size = 0.3) between glycaemia measures (mean and variability) and birth weight at a significance level of *p* < 0.05. Repeated CGM measurements (four one-week periods per participant) were accounted for using a cluster size of four and assuming an interclass correlation (ICC) of 0.5. A drop-out rate of 30% was assumed, in the sense that 30% of all measurements would be missing. The sample size was decided considering adjustment for four variables in the analysis. A Bonferroni correction will be applied to control for multiple comparisons, resulting in a 2.5% test-wise significance level.

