### 2.3. Objectives

This trial is designed to show with 80% power a linear association between mean glycemia or glycaemic variability and birth weight in a pregnancy after MBS. The hypothesis is that an altered metabolic profile including an altered glucose metabolism (with increased time spent in hypoglycaemia and greater glycaemic variability) and altered metabolomics during pregnancy after MBS contribute to the increased risk of adverse pregnancy outcomes such as SGA and preterm delivery. In addition, we hypothesise that concentrations of branched-chain and aromatic amino acids, and unsaturated lipids in the third trimester of pregnancy, are lower in pregnant women with MBS, and that this is also associated with a lower birth weight.

This study aims to evaluate whether biomarkers derived from CGM and metabolomic profiling in pregnancies following MBS are associated with foetal growth and newborn body composition.

The following specific aims will be addressed.

Primary aim: To determine whether altered glucose metabolism (including lower mean blood glucose levels, hypoglycaemia, and glycaemic variability) measured by CGM in pregnancy after MBS is related to delayed foetal growth.

Exploratory objectives:To compare glucose metabolisms between pregnant women after MBS and age- and BMI-matched pregnant women without MBS.To determine whether metabolic alterations are associated with delayed foetal growth in pregnant women after MBS compared to pregnant women without MBS, and, in particular, which metabolites are related to adverse outcomes in pregnancy.To determine whether there are differences in glucose metabolism and other metabolites (by using metabolomics) between RYBG and SG.To determine the impact of MBS on the body composition of newborns.To determine the accuracy of CGM compared to the self-monitoring of capillary blood glucose (SMBG) to screen for GDM in pregnant women with MBS.

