#### 2.3.1. Primary Outcome

In the surgical group, we will assess mean glycaemia as a continuous outcome variable, glycaemic variability (standard deviation) as a continuous outcome variable, and birth weight as a continuous explanatory variable. Linear mixed models will be used for the primary outcome analysis. The outcome variables will be measured at four time points for each subject. Confounders will be added to the model as covariates.

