#### 2.9.2. Statistical Methods

##### Primary and Secondary Analyses (MBS Group)

The primary analysis will be performed using linear mixed models, adjusted for confounders. Mean glycemia refers to the mean interstitial glucose level measured via CGM throughout pregnancy. Glycaemic variability reflects fluctuations in blood glucose levels and is quantified using variables such as SD, CV, and MAGE derived from CGM. Repeated measurements will be used for the primary outcome analysis, with mean glycemia and glycaemic variability treated as continuous outcome variables, and birth weight as the explanatory variable. To account for clustering due to repeated measures, linear mixed models will be used with a random intercept for the subject. Confounders such as smoking, hypertension, nutrient deficiencies, insufficient gestational weight gain, and time from surgery will be added to the model as covariates to determine the independent association between birth weight and glycaemic parameters. Variables will be considered confounders if they are associated with both birth weight and glycaemic parameters. Linear slopes with 95% confidence intervals will describe the association between glycaemic parameters and birth weight. No specific action is taken to deal with missing CGM results given the fact that the analysis model is likelihood-based and known to provide unbiased results under the fairly general assumption of missingness at random [42]. Statistical analysis will be performed by SAS version 9.4; all tests will be two-sided with significance set at *p* < 0.05.

Secondary outcomes, including time spent <54 mg/dL and hyperglycaemic thresholds (>120 mg/dL and >140 mg/dL), will be analysed analogously.

Third, associations between glycaemic patterns and binary neonatal outcomes, including SGA and birth defects, will be assessed similarly using linear models for repeated measurements. Mean differences with 95% confidence intervals will be estimated between cases with and without the specified adverse outcome.

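### The two primary tests use single-step Bonferroni, which is valid; Holm's procedure would give the same 5% family-wise control and more power if both associations are real

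*Protocol article*

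**What the plan says.** Section 2.3.1 of the protocol article sets two primary outcome variables in the surgical group: "we will assess mean glycaemia as a continuous outcome variable, glycaemic variability (standard deviation) as a continuous outcome variable". Birth weight is the explanatory variable for each, so there are two primary tests.

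Section 2.9.1 divides the 5% between them: "A Bonferroni correction will be applied to control for multiple comparisons, resulting in a 2.5% test-wise significance level". No step-down rule is mentioned, so each test stays at 2.5% whatever the other shows. The same section gives the power statement, with one effect size for both measures: "The study provides 80% power to detect a moderate association (effect size = 0.3) between glycaemia measures (mean and variability) and birth weight".

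The objective in section 2.3 joins the two measures by 'or'. The trial is "designed to show with 80% power a linear association between mean glycemia or glycaemic variability and birth weight".

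Section 2.9.2, under the primary and secondary analyses, says that "all tests will be two-sided with significance set at" p < 0.05, and describes slopes with 95% confidence intervals. It does not repeat the 2.5% level.

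**The concern.** With two hypotheses, single-step Bonferroni is stricter than it needs to be. If one null has been rejected at 2.5%, only one null remains that could be falsely rejected, and it can be tested at the full 5%. Holm's step-down procedure does this. It rejects whatever Bonferroni rejects and sometimes more, holds the family-wise error at 5% under any dependence between the tests, and needs no further participants or assumptions.

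What is at stake is the chance of confirming each measure in its own right, and of confirming both. The article treats both as real candidates: the effect size of 0.3 is planned for mean and variability alike, and the Discussion argues specifically for preventing glycaemic variability. A near miss on the second measure, with a p-value between 0.025 and 0.05, would count as not confirmed under the planned rule even when the first had clearly succeeded.

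**Working it through.** **Inputs from section 2.9.1.** Effect size 0.3 (read as a correlation); 80% power; test-wise level 2.5%, two-sided (sidedness from section 2.9.2). Repeated measurements "were accounted for using a cluster size of four and assuming an interclass correlation (ICC) of 0.5". Missing data: "A drop-out rate of 30% was assumed, in the sense that 30% of all measurements would be missing". Covariates: "The sample size was decided considering adjustment for four variables in the analysis".

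**Step 1: reproduce n = 95.**
- Sum of normal quantiles: z(0.9875) + z(0.80) = 2.241 + 0.842 = 3.083.
- Fisher z of the effect: atanh(0.3) = 0.3095.
- Independent observations: (3.083 / 0.3095)² + 3 = 102.2; plus 4 covariates = 106.2.
- Design effect: 1 + (4 - 1) × 0.5 = 2.5.
- Women: 106.2 × 2.5 / 4 / 0.70 = 94.8, so 95.

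The same formula at 5% gives 88.9 × 2.5 / 4 / 0.70 = 79.4. The stated 80% is therefore per-test power at 2.5%, and that is the baseline for the comparison.

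**Step 2: Holm in closed form, independent test statistics, both effects at 0.3.**
- Each statistic has mean 3.083. Its power at a 5% level is Φ(3.083 - 1.960) = 0.869, the ceiling for any gain.
- The chance that one p-value lies between 0.025 and 0.05 is 0.869 - 0.800 = 0.069.
- Per-test power under Holm: 0.80 + 0.80 × 0.069 = 0.855.
- Both rejected: Bonferroni 0.80² = 0.640; Holm 0.640 + 2 × 0.80 × 0.069 = 0.751 (unrounded inputs).
- At least one rejected: 1 - 0.20² = 0.960 under either procedure.

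**Step 3: other correlations.** The article gives no correlation between the two test statistics, so the values below are assumptions. They come from simulated bivariate normal statistics, each with mean 3.083, with signs set so that both planned effects are positive.

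| Correlation | Per test, Bonferroni | Per test, Holm | Both, Bonferroni | Both, Holm | At least one, either procedure |
|---|---|---|---|---|---|
| -0.5 | 80% | 86.5% | 60.9% | 73.9% | 99.2% |
| 0 | 80% | 85.5% | 64.0% | 75.1% | 96.0% |
| 0.3 | 80% | 85.0% | 66.6% | 76.5% | 93.4% |
| 0.5 | 80% | 84.6% | 68.8% | 77.8% | 91.3% |
| 0.7 | 80% | 84.1% | 71.3% | 79.5% | 88.7% |
| 0.9 | 80% | 83.2% | 75.0% | 81.5% | 85.0% |

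**Step 4: only one association real.** Power for the real one under Holm is 80.2% at correlation 0, 80.1% at 0.5 and 80.0% at 0.9. In closed form at correlation 0: 0.80 + 0.025 × 0.069 = 0.802.

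**Step 5: error control under Holm.**
- Both nulls true: family-wise error 4.95% at correlation 0, 4.63% at 0.5 and 3.63% at 0.9.
- One null true: it is falsely rejected in 4.5%, 4.2% and 3.8% respectively. At correlation 0 this is 0.025 + 0.025 × 0.80 = 0.045.

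**The case against.** The strongest reply is that nothing here is wrong. Bonferroni is valid, its level is stated, and the sample size was built for it. That stands in full. A reader might infer a type I error fault or an underpowered study; the article supports neither, since n = 95 reproduces at 2.5%.

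Second, the objective in section 2.3 is worded with 'or'. If success means at least one association, Holm changes nothing: that chance is identical under both procedures at every correlation. This stands. The gain is confined to per-test power and to confirming both.

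Third, a reader might set the 61-71% chance of confirming both against the quoted 80% and conclude that the plan misses its target. It does not. Section 2.9.1 gives 80% per measure at the test-wise level, section 2.3 gives it for either measure, and no section promises it for both.

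Fourth, the 80% baseline is itself cautious, because n applies the design effect for four measurements and then removes 30% of them. With an average of 2.8 measurements, the design effect is 1 + 1.8 × 0.5 = 1.9, and 95 × 2.8 / 1.9 = 140 effective observations. The mean of the statistic is then √(140 - 7) × 0.3095 = 3.57, and power at 2.5% is Φ(3.57 - 2.24), about 91%. Holm would then add about 2.6 to 3.5 points per test (correlation 0.7 to 0). This makes the gain smaller on that reading but leaves its direction unchanged.

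Fifth, 97.5% intervals match single-step Bonferroni decisions exactly, which has value when slopes are the main result. Holm loses that match for the second test. The loss is real but small, and the article currently plans 95% intervals, which do not match a 2.5% test either.

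Last, a more liberal rule adopted after data have accrued needs care. That governs when the change should be made; it is no argument against Holm itself.

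**Conclusion.** The point holds as an avoidable loss of efficiency. If both associations are real at 0.3, which is the article's own planning assumption, Holm adds about 4 to 6 percentage points per test and about 8 to 13 points to the chance of confirming both, for correlations from -0.5 to 0.7. At 0.9 the per-test gain is about 3 points. If only one association is real, the gain is at most about 0.2 points. Under the 'or' objective the chance of success does not change.

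The figures rest on reading 0.3 as a correlation, on the 80% baseline of section 2.9.1, on approximately normal test statistics, and on assumed correlations between them. The validity of Holm and the fact that it never loses power to Bonferroni depend on none of these.

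**What to change.** Before the data are analysed, replace the Bonferroni sentence in section 2.9.1 with: *The two primary p-values will be tested by Holm's procedure at a family-wise 5%: the smaller at 2.5% and, if rejected, the larger at 5%.* Keep n = 95 and describe 80% as a lower bound on the power of each test.

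Amend section 2.9.2 to match. For the two primary tests, the general p < 0.05 rule should defer to Holm, and the 95% intervals for the two primary slopes should be reconciled with it, for example by 97.5% intervals as a conservative display.

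The cost is one replaced sentence, a short edit to section 2.9.2, and an amendment reported to the ethics committees as section 2.9.4 requires. No more women or measurements are needed. The one statistical drawback should be stated: when the second test is rejected with a p-value between 0.025 and 0.05, its 97.5% interval will still include zero.
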